#### Intervention

The educative intervention is based on the format developed during our Phase-1 project, i.e. a two-day preceptorship combining theoretical and practical CME, and includes both plenary and nurse- or PCP-specific sessions. At the beginning of our Phase 2 project, we thoroughly reviewed the content of the preceptorship according to expert opinions relevant literature and comments/suggestions from Phase-1 participants. All important topics concerning CCPGO recommendations are covered, such as initial evaluation of patients (including readiness for change), nutritional approach, physical activity, behaviour modification and support to patients, pharmacotherapy, indications for bariatric surgery, obesity in children and adolescents etc. Training is divided into two days that are provided approximately 1 month apart in order for participants to put new knowledge into practice and better identify areas to emphasize during the 2^nd^ day. More than half of the time is devoted to the observation of real patient encounters and case discussions. Sessions are given by members of our research team who are also involved in the Centre Hospitalier Universitaire de Sherbrooke (CHUS) obesity clinic: endocrinologists, pediatric endocrinologist, dietician, kinesiologist and psychologist, according to their field of expertise. The general objective of the preceptorship is to increase self-efficacy and optimize interventions of health professionals regarding obese and overweight patients in complementarity with specialized interdisciplinary resources of the CHUS obesity clinic.

The intervention group also has access to the virtual community previously described, including the web site posting information for health professional and patient tools, monthly virtual meetings where advances in obesity management and difficult cases are discussed, and a discussion forum for participants and obesity experts.

Following expressed needs of participants at the end of Phase-1, we are also providing on-site coaching sessions for FMG participants every three months. They consist of 1 hour discussions with the dietician or kinesiologist of our team who visits the FMG to solve problems with web-site use, solve difficult cases, discuss use of program tools and explore practice changes. The objective is to help participants integrate the virtual community in their practice and answer their clinical questions.

The FMGs allocated to the control group are only provided with a copy of the current Canadian guidelines for the treatment of obesity, diabetes, dyslipidemia and HTN [4,40–42].

### Ethical considerations

The research project was reviewed and approved by the appropriate institutional Research Ethics Review Boards according to applicable laws and Tri-Council Policy Statement. Research participants (both patients and health professionals) were duly informed and consent was obtained in writing prior to participation. However, as mentioned above, subjects were not informed regarding the intervention. They were told that the objective of the study was to evaluate lifestyle management in primary care settings and its evolution over time. In order to minimize deceptive ethical issues, all participants will be fully informed of all the objectives and interventions of the study after their final assessment, with appropriate debriefing. Initial contact of potential candidate patients was performed by FMG clerical personnel who gave them a pamphlet with information on the study and obtained their signed consent to have their chart reviewed by the research team and to be contacted if needed. Ethical considerations raised by the research are mainly confidentiality issues. All data will be coded, archived for at least 5 years and then destroyed.

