**Methods/Design:**

Ten FMGs will be approached for a practice monitoring project and will be randomised to receive the intervention developed in our previous project or will only be provided clinical practice guidelines. In the participating FMGs, we will enrol 22 patients per FMG with weight related targeted disease and 24 patients with regular follow-up. These patients will be evaluated for the care they received regarding screening and/or management of obesity using medical chart reviews, and will fill out a questionnaire on their lifestyle and satisfaction. They will also be examined for anthropometric measures, vital signs, blood markers for chronic diseases and physical fitness. The same patients will be assessed again after 18 months. The impact of the program on health professionals will be evaluated at baseline, and at 1 year. Qualitative data will also be collected from both professional and patient participants. Direct and indirect costs and QALYs will be evaluated as indicators of cost-effectiveness.

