**Summary of design of the proposed research project.**

#### Study participants

The Integrated University Health Network, known as the RUIS (*Réseaux universitaires intégrés de santé*), of *Université de Sherbrooke* caters to a population of over 1 million people, encompassing a vast territory including Sherbrooke and Montérégie areas. A pool of at least 35 FMGs in this coverage area did not participate in our Phase-1 project. We will enroll a total of 10 of these FMGs in Phase-2, from which 4-10 members (including at least 2 PCPs and 1 nurse) will participate in our study. When we will initially contact FMGs, we will propose to them a study assessing lifestyle management in primary care and its evolution over time. When we will be in contact with 2 interested FMGs, we will randomize them to the intervention or control groups. The first FMG will then be offered to participate in our obesity management system with preceptorships and virtual learning community. The control FMG will be offered practice monitoring without being aware of the intervention. Participants of each group will sign different consent forms.

As much as possible, we plan to evaluate participants from FMGs pairs of intervention and control groups concomitantly in order to avoid bias related to time of evaluation (due to seasonal effects on weight, campaigns of health promotion, high-impact scientific publications, etc.). Within each FMG, adult patients who present for follow-up will be offered by FMG clerical personnel to have their chart accessed by our team and to be contacted if eligible for the project. If they consent, their chart will be screened to verify if they had, during the past 2 years, at least 4 documented visits for the targeted disease group and at least 2 visits for the regular follow-up group, and if continued follow-up is planned or highly probable in the next 18 months. We aim to include in our study 22 patients per FMG in the targeted disease group, and 24 patients per FMG in the regular follow-up group (total of 460 patients). Patient numbers will be prospectively accrued within each patient category during the recruitment period and before preceptorship delivery for the intervention group, until targeted numbers are achieved. In order to minimize important potential biases, patients will be kept blinded regarding their FMG group and the study objectives related to the evaluation of this intervention.

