### Variables and research tools

#### Evaluation of patients

All evaluations will take place at baseline and after 18 months in order to allow sufficient time following the intervention to monitor changes in practice. Although very long term weight maintenance cannot be assessed during that period, we could eventually continue following patients on a longer term as part of future projects.

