#### Medical history and lifestyle interventions

At the end of the study for each study site, thorough medical chart review will be performed using a standardized evaluation grid, also verifying medical and surgical history and medications for the 18 months before and after baseline evaluation of patients. Evaluations and interventions that are proposed to patients will be compared to that proposed in the CCPGO algorithm, and evolution of patients’ weight during the observation period will be recorded.

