#### Evaluation of health professionals (PCPs and nurses)

All evaluations will take place at baseline, T1 (1 month after the preceptorship for the intervention group and 1 month after baseline for the control group) and 12 months after T1 in order to compare the data collected during our Phase 1 study and to compare intervention and control groups. The same questionnaires that we developed and validated will be used to evaluate Aim 3 of this proposal. We have slightly modified some tools based on the results of our Phase 1 project. Results will be correlated to patients’ outcome.

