### Sample size, data analysis and interpretation

According to AIM 1, our primary variable of interest is the proportion of obese or overweight subjects with HTN, DM2 or IGT who will lose least 5% of their initial weight after eighteen months. Assuming that 30% drop-out or provide incomplete data, our study needs to recruit 220 obese or overweight subjects with HTN, DM2 or IGT in order to achieve 80% power (using chi-square) to detect a doubling in the proportion of those who will lose at least 5% of their initial weight, based on a proportion of 21% in the control group (which is the average proportion observed in the control groups of two of our previous studies) [32,33,67] and 42% in the intervention group (which represent half of the average benefits found in these two studies compared to control groups) (***AIM 1***). Similarly, 240 unselected patients provided 80% power (using Fisher’s-exact test because of small minimum expected cell size) to detect an improvement of the proportion of these patients who have a reported measure of BMI from 80% in the control group (based on reported practice in our previous participants) to 95% in the intervention group (which is close to the 100% recommended by the CCPGO) (***AIM 2***). For AIM 2, our primary variable of interest is the proportion of unselected patients who have a reported measure of BMI, which defines obesity according to WHO and is therefore essential for the screening of obesity.

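### Debriefing participants after their own final assessment would, read plainly, unmask control professionals nominally 5 months before their patients' 18-month outcomes, putting mainly the chart-based outcomes at risk

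*Protocol article*

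**What the plan says.** **Masking.** Under Study participants, the Protocol article states: "The control FMG will be offered practice monitoring without being aware of the intervention". The same section keeps patients blinded to their FMG's group and to the objectives that concern the intervention, and gives limiting bias as the reason.

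**Debriefing.** Ethical considerations first makes clear who the participants are: "Research participants (both patients and health professionals) were duly informed". It then sets the time of disclosure: "all participants will be fully informed of all the objectives and interventions of the study after their final assessment". No other sentence in the article holds back the professionals' debriefing until their patients have finished.

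**Professionals' schedule.** Assessments are at baseline, at T1, and a year after T1. For controls this reads "1 month after baseline for the control group) and 12 months after T1". The abstract is looser: "The impact of the program on health professionals will be evaluated at baseline, and at 1 year".

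**Patients' schedule.** "All evaluations will take place at baseline and after 18 months". The Aim 1 primary variable is the proportion who "lose least 5% of their initial weight after eighteen months". The chart review covers history and "medications for the 18 months before and after baseline evaluation of patients". The Aim 2 primary variable is the proportion of regular follow-up patients with a reported BMI.

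**The concern.** The two kinds of participant finish at different times, and the debriefing rule follows the participant rather than the site. A control physician or nurse who has completed the last questionnaire may be told that the trial compares trained with untrained practices on obesity screening and management. That same clinician is still making the chart entries on which the control arm is judged.

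A BMI entry or a planned weight intervention can be added at a single visit, so even a short unmasked period could move some control patients from failure to success. The change would arise in one arm only and most likely shrink the measured difference.

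There is a second route. Patients are accrued until the targets are reached, so their 18-month dates are staggered. Those who finish first may be debriefed while other patients of the same FMG, and its clinicians, are still under observation.

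**Working it through.** **1. Nominal gap.** Inputs: control T1 at month 1 and last assessment 12 months later (Evaluation of health professionals); patient outcome at month 18 (Evaluation of patients; Sample size).

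- Professionals' last scheduled assessment: 1 + 12 = month 13.
- Gap if the two baselines coincide: 18 − 13 = 5 months, and 5/18 = 28% of patient follow-up.
- On the abstract's wording (1 year): 18 − 12 = 6 months.

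**2. Dependence on the baselines.** The article does not say how patient and professional baselines are aligned. It says only that patients are accrued before the preceptorship in the intervention group. Let L be the number of months by which a patient's baseline precedes the professionals' baseline. Then gap = 18 − L − 13 = 5 − L, with a floor of zero.

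| L (months) | Gap (months) |
|---|---|
| −3 (patient enrolled later) | 8 |
| 0 | 5 |
| 3 | 2 |
| 5 | 0 |

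So 5 months is one point in a range that includes zero. It is not a minimum.

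**3. Which outcomes can move in that time.**

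- *Recorded BMI and planned interventions:* one visit is enough. At the minimum visit rate required of regular follow-up patients (2 in 2 years), 5 months yields 2 × 5/24 = 0.42 visits per patient. More frequent attenders give more opportunity.
- *5% weight loss:* this takes longer. The programmes described in the Background report 33% to 55% of patients reaching it after 12 months of structured management. A debriefed clinician has had no preceptorship, portal or coaching.

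**4. What a small shift in recorded BMI would cost (illustration).** The plan's own figures for Aim 2 are 80% against 95%, 240 patients, Fisher's exact test, 80% power. The 30% loss is stated for Aim 1; applying it to Aim 2 is an assumption. It gives 240 × 0.70 = 168, or 84 per arm. Exact two-sided 5% Fisher power, ignoring clustering:

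| Control rate | 84 per arm | 120 per arm (no loss) |
|---|---|---|
| 80% (plan) | 81.7% | 93.5% |
| 82% (assumed) | 71.4% | 86.5% |
| 85% (assumed) | 50.8% | 67.4% |

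The first row at 84 per arm is consistent with the plan's 80%. The shifted rates have no source in the document. A rise to 85% means that a quarter of the 20% without a BMI gain one late (80% + 0.25 × 20% = 85%). At 0.42 visits per patient, about 0.25/0.42 = 60% of those visits would have to yield a first entry. The 85% row is therefore demanding at the minimum visit rate. The 82% row needs a tenth of the patients without a BMI to gain one.

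**The case against.** **Masking is already partial.** Control FMGs receive the Canadian obesity guidelines, and professionals in both groups answer the same tools on attitudes to obesity management, obesity knowledge and weight-management vignettes. They have strong cues from the start. This stands, and it limits what debriefing adds. It does not remove the point: the guidelines also cover diabetes, dyslipidemia and hypertension, the knowledge test mixes in other topics, and participants are told the study concerns lifestyle management. Full debriefing would add the hypothesis and the existence of a comparison.

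**The rule can be read collectively.** The final assessment could mean the end of the study or of the site; the chart review is indeed placed at the end of the study for each site. The professionals' interviews carry no date and might count as their final assessment. The sentences just before the rule speak of subjects, which might mean chiefly patients. These readings are possible, but the article states none of them. If one is intended, the amendment only makes it explicit.

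**Stronger readings are not supported.** A reader might infer that at least 5 months of every control patient's follow-up is unmasked. That would require aligned baselines, or patients enrolled later than the professionals, and the article states neither. A reader might also infer that both primary variables are contaminated. A late effect on 5% weight loss is much less plausible than one on BMI charting, and nothing in the article quantifies either. Disclosure from patient to clinician is a possibility, not something the article shows will happen.

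**Bias would probably run towards no difference.** This is the likely direction, so a false positive is not the main worry. Loss of power in a trial planned at 80% is still worth avoiding.

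**Conclusion.** The point holds in a limited form. As written, the debriefing rule covers professionals and is triggered by their own last assessment. Followed on its plain reading, it breaks the masking of control FMGs while patient outcomes are still accruing.

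The gap is nominally 5 months (6 on the abstract's wording), shrinks to zero for patients whose baseline came at least 5 months before the professionals', and grows for those enrolled later. The outcomes mainly exposed are recorded BMI and planned weight interventions. Dilution is the likely direction.

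The amount of bias cannot be derived from the document; the power figures above only show how sensitive Aim 2 would be to an assumed shift. The conclusion rests on two readings: that the final assessment is each participant's own, and that it falls at the scheduled questionnaire visit. This is an avoidable risk in one arm that is cheap to remove, not a demonstrated contamination of the trial.

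**What to change.** Amend the sentence in Ethical considerations so that health professionals and patients are debriefed only after the last 18-month patient assessment is complete and the chart window has closed in both FMGs of the randomised pair. Tying it to the pair rather than the single FMG also protects the partner practice, and it closes the route through patients who finish early.

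The change is one sentence in the protocol, with ethics approval and matching wording in the consent and debriefing material. Sample size, visits and measurements are unchanged, and the period after a professional's debriefing that falls inside patient follow-up becomes zero. The cost is that professionals and early-finishing patients wait some months longer for full disclosure, which the ethics boards would need to accept.

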### Variables and research tools

#### Evaluation of patients

All evaluations will take place at baseline and after 18 months in order to allow sufficient time following the intervention to monitor changes in practice. Although very long term weight maintenance cannot be assessed during that period, we could eventually continue following patients on a longer term as part of future projects.

#### Anthropometric measures and vital signs

Weight will be measured in patient participants by a standard calibrated scale in kilograms to the nearest decimal (0.1 kg) wearing indoor clothing, with empty pockets and without shoes. Height will be measured with a stadiometer in meters to the nearest millimeter (0.001 m), without shoes. Waist circumference will be measured twice with a measuring tape at the top of the upper iliac crest, at the end of a normal expiration, as recommended; we will record the average of 2 measures with less than 1 cm variation [4,43]. Lean body mass, fat mass (in kg) and percent body fat will be measured by standing electric bioimpedance using a Tanita weight scale (model TBF-300A). Standing electric bioimpedance was shown to be reliable compared to underwater weighing and to conventional supine tetrapolar bioimpedance [44–46]. Blood pressure and pulse rate will be measured after five minutes of rest, in the sitting position. The average of two measurements will be used for analysis.

#### Medical history and lifestyle interventions

At the end of the study for each study site, thorough medical chart review will be performed using a standardized evaluation grid, also verifying medical and surgical history and medications for the 18 months before and after baseline evaluation of patients. Evaluations and interventions that are proposed to patients will be compared to that proposed in the CCPGO algorithm, and evolution of patients’ weight during the observation period will be recorded.

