#### Changes in practice

A services evaluation grid will be completed with the administrator of the FMG in order to assess practice organization. Also, individual practice of participants will be assessed using clinical vignettes describing a patient presenting for a routine exam or for weight management. This tool was used in our previous study to demonstrate changes in reported management of obesity. A qualitative in-depth analysis of participants perceptions of the program will be performed using semi-structured interviews in each FMG [36]. This will increase our understanding of their experience, inter-professional collaboration, satisfaction with the program, change process and further identify and detail strengths and areas for potential improvement.

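### Stated masking covers patients and control FMGs but not the people who abstract charts or score judged outcomes, and review by site exposes the arm to anyone who knows the allocation

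*Protocol article*

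**What the plan says.** The article names two protections, both under Study participants. For patients: "patients will be kept blinded regarding their FMG group and the study objectives related to the evaluation of this intervention". For control practices: "The control FMG will be offered practice monitoring without being aware of the intervention". It states no masking for anyone who abstracts charts, rates care, scores sheets or examines patients.

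Under Intervention, the programme is delivered from within the research team. On the preceptorship: "Sessions are given by members of our research team who are also involved in the Centre Hospitalier Universitaire de Sherbrooke (CHUS) obesity clinic". On the three-monthly coaching: "They consist of 1 hour discussions with the dietician or kinesiologist of our team who visits the FMG".

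Charts are also handled by the team. Study participants has patients agree to the team accessing their chart, and Ethical considerations describes the consent as covering chart review by the research team.

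The section Medical history and lifestyle interventions sets the timing of the outcome review: "At the end of the study for each study site, thorough medical chart review will be performed using a standardized evaluation grid". It spans 18 months on either side of the baseline evaluation. The same section adds: "Evaluations and interventions that are proposed to patients will be compared to that proposed in the CCPGO algorithm". Under Changes in practice, "individual practice of participants will be assessed using clinical vignettes describing a patient presenting for a routine exam or for weight management". The knowledge questionnaire includes short-answer items (Knowledge and expertise on obesity management). None of these sections names the reviewer, rater or scorer.

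**The concern.** Some outcomes need a person to decide what a record or an answer means. Whether a chart note amounts to a planned initial weight intervention is one, and it is listed under Primary aims for both patient groups. Conformity with the CCPGO algorithm, vignette responses and short answers are others.

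If the person deciding knows the arm, slightly more generous reading of intervention records would appear as a programme effect. The multivariate analyses under Sample size, data analysis and interpretation adjust for baseline differences, confounders and FMG clustering. They could not remove such an error: each FMG belongs wholly to one arm, so leniency that follows the arm coincides with the treatment contrast.

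**Working it through.** **1. Who is masked.** Patients: yes. Control FMGs: kept unaware of the intervention. Chart abstractors, conformity raters, scorers and examiners: nothing is stated.

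**2. Where the roles meet.** Training and coaching: members of the research team. Chart access and review: the research team, by the consent wording. Conformity, vignettes and short answers: nobody named. The overlap is therefore documented for the team, not for individuals.

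**3. What review by site reveals.** FMGs are randomised in pairs, and every patient in an FMG shares its arm. Each FMG contributes 22 + 24 = 46 patients, and 10 × 46 = 460 in total. Knowing one FMG's allocation therefore reveals the arm of 46 charts, or 46/460 = 10% of the trial. Chart dates show whether an entry falls before or after baseline.

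**4. Exposure by outcome.**
- Initial intervention planned (Aims 1 and 2): read from charts, can need judgement; exposed.
- CCPGO conformity: a comparison made by a rater; exposed.
- Vignettes and short-answer items: scored by someone; exposed.
- Weight loss of at least 5% (main variable, Aim 1): calibrated scale read to 0.1 kg; little exposed.
- Recorded BMI (main variable, Aim 2): present in the chart or not; little exposed.
- HbA1c and apolipoproteins: laboratory values; little exposed.
- Six-minute walk: follows a published protocol, but masking of the tester is not stated.

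**5. Possible size, on assumed inputs.** The article gives no share of ambiguous charts and no planned effect for an intervention being planned. Let *a* be the share of charts with an ambiguous note, and let g₁ and g₀ be the proportions of these accepted in the intervention and control arms. With no true difference, the spurious difference is *a* × (g₁ − g₀).
- Milder case: 0.20 × (0.60 − 0.40) = 0.04, or 4 points.
- Stronger case: 0.30 × (0.70 − 0.30) = 0.12, or 12 points.

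**6. The plan's own figures.** They are not in dispute.
- Aim 1 (21% vs 42%, two-sided 5%, 80% power, no continuity correction) needs 76 per arm, or 152 evaluable. 152/0.70 rounds up to 218, against the stated 220.
- Aim 2: if the 30% loss also applies here, 240 × 0.70 = 168, or 84 per arm. Exact Fisher power for 80% vs 95% is 81.7%, against the stated 80%.

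**7. What a shift does to a test, for scale only.** Take 84 per arm, a true rate of 80% in both arms, and clustering ignored. Fisher's test rejects 3.1% of the time with no shift, 4.0% with a 2-point shift in one arm, 9.6% with 5 points and 36.7% with 10 points. The 80% is the recorded-BMI rate, and that item is little exposed. These figures show how fast false positives rise with a shift of this kind; they are not a forecast for any outcome in this trial.

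**The case against.** The case on the other side is substantial.

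- **No rater is named.** A reader might infer that the trainers and coaches themselves review the charts and score the vignettes. The documents do not support that. The sections on chart review and vignettes are in the passive, and the consent wording comes from the account of first contact with patients. The overlap is possible and not excluded, but it is not stated. This stands.
- **Masking is not confined to patients.** Control FMGs are also kept unaware of the intervention. This stands.
- **The main variables are hard to bias.** A reader might infer that the trial's headline comparisons are compromised. They rest on a calibrated scale and on whether a BMI is recorded. Being listed first under Aim 1 does not make a planned intervention the main variable. This stands.
- **A standardized grid is used.** It reduces variation between raters but does not hide the arm, so this stands only in part.
- **An article may leave assessor masking to the full protocol.** Silence alone would indeed be no finding. But this article lists its protections against bias, places chart access and review with the team that runs the programme, and fixes a review by site in a trial randomised by site. That arrangement can be judged as written. If the full protocol already separates the roles, one sentence settles the matter.

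**Conclusion.** The point holds for the judged outcomes only. As written, nothing keeps a person who knows the allocation from abstracting charts, rating conformity, or scoring vignettes and short answers, and the later adjustment could not correct the resulting bias.

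Its size cannot be obtained from the article. The 4 to 12 points rest wholly on assumed shares of ambiguous charts and assumed gaps in acceptance; the upper end needs ambiguous notes to be accepted more than twice as often in one arm (70% vs 30%). These figures should not be set against the improvement planned for recorded BMI, which is a different and largely factual endpoint. No sample size, power or other stated figure changes. It is a worthwhile and inexpensive correction, not a threat to the two main variables.

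**What to change.** With existing staff, state that:
1. Team members who teach or coach do not abstract charts, rate CCPGO conformity or test patients.
2. Chart abstractors are not told the FMG's allocation, and the grid carries a rule, set before review starts, for what counts as an initial intervention planned.
3. Vignettes and short-answer sheets are coded and scored in mixed order across arms and time points, by someone who sees only the code.

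The cost is some division of tasks, a coding step, and a delay in scoring until sheets from both arms and all time points can be mixed. A second rating of de-identified chart extracts is not needed. A chart that mentions programme tools may still reveal the arm; the pre-set rule limits what that knowledge can do, but does not remove it.
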